### Phase 3: Pilot Trial of the pCGA Implementation Package

#### Study Design

We will conduct a pretest-posttest pilot study of the implementation package over 10 months, conducted at the clinic level at 2 busy academic medical center surgical subspecialty clinics performing major abdominal surgery (selecting one that does not routinely refer for pCGA in addition to one that does routinely refer). We will collect baseline prepilot data via retrospective chart abstraction from the year before the intervention. After an implementation rollout period of 2 months, postintervention data will be collected over 10 months. Specifically, we will assess outcomes according to the RE-AIM framework [38], using chart abstraction for patient-level data and simple self-reported surveys for the health care professionals. We hypothesize that a user-designed implementation package will improve the reach and adoption of the pCGA compared to the historic baseline.

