##### Health Care Professionals

Consistent with implementation research, health care professionals using the pCGA implementation package are considered study participants [76]. As participants from among the health care professionals who participated in the co-design will be recruited for the pilot trial, they will be familiar with the intervention. Surgeons referring patients from the 2 clinics (n=12) and health care professionals engaged at the pCGA clinic (n=10) will be asked to participate in the pilot.

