#### Outcomes

The primary outcomes of this pilot trial will be reach and adoption, assessed using the RE-AIM framework [38] (Table 2). Reach refers to the percentage and characteristics of older adults receiving the pCGA intervention, while adoption accounts for those health systems and health care professionals who refer patients for, or deliver, the pCGA [38,92]. Of note, implementation in the RE-AIM framework refers to fidelity, or the extent to which an intervention is delivered as intended. We will expand the implementation domain to include measures of fidelity, as defined by NIH Best Practices [40], as well as feasibility, acceptability, and appropriateness according to the taxonomy of implementation outcomes developed by Proctor et al [93]. The primary effectiveness outcome will be postoperative length of stay, which is an easily measured, continuous outcome variable commonly used in the surgical literature on pCGA [29]. We will collect exploratory measures to inform the selection of effectiveness outcomes for a future implementation-effectiveness trial. These exploratory outcome measures will include (1) a composite of death or postoperative complication events; and (2) data points relevant to the pCGA, including a cognitive outcome (postoperative delirium), functional outcome (discharge destination to home, rehabilitation, or skilled nursing), nutritional outcome (discharge diet, albumin level, and weight at discharge), and polypharmacy (Beers criteria discharge medications [79], anticholinergic burden score [78], and number of opioid pain pills prescribed at discharge).

**Table 2 table2:** The reach, effectiveness, adoption, implementation, and maintenance (RE-AIM) domains and associated outcome measures.

Domain	Definition	Measurement
Reach	The percentage and characteristics of older patients who receive pCGA^a^ before abdominal surgery	Referred ÷ potentially eligible patients Comparison of referred ÷ eligible patients by age, sex, race, ethnicity, BMI, and zip code Target reach: >50% referral of eligible pCGA patients per clinic
Effectiveness	The improvement in clinical outcomes from pCGA receipt	Primary: postoperative length of stay Secondary: 30-day morbidity and mortality (refer to Chart Abstraction section)
Adoption	Surgeon intent, decision, and action to refer eligible patients for pCGA	Percentage of surgeons referring ÷ total surgeons in the pilot clinic Target adoption: >75% of surgeons achieving >50% referrals

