Implementation: fidelity	Multifaceted outcome that includes (1) treatment *dose* or amount of intervention delivered, (2) quality or content of intervention delivered by health care professionals, and (3) treatment receipt and enactment by patients (NIH^b^ Best Practices) [40]	(1 and 2) Percentage of completed pCGA components, as abstracted from the medical record at pCGA visit (3) Completion of pCGA recommendations, as abstracted from the medical record at the time of surgery Target fidelity: >90% of pCGA components completed
Implementation: feasibility^c^	Perceived ease of use of pCGA implementation package	Feasibility of intervention measure (4-item survey) [94]
Implementation: acceptability^c^	Satisfaction with the pCGA implementation package	Acceptability of implementation measure (4-item survey) [94]
Implementation: appropriateness^c^	Fit and relevance of pCGA implementation package	Intervention appropriateness measure (4-item survey) [94]
Maintenance	The extent to which pCGA use is sustained over the pilot period	Trends in reach, adoption, and implementation outcomes will be evaluated at 6 months and 12 months

^a^pCGA: preoperative comprehensive geriatric assessment.

^b^NIH: National Institutes of Health.

^c^The feasibility, acceptability, and appropriateness of the pCGA implementation package will be assessed via surveys administered to health care professionals (eg, surgeons, geriatricians, advanced practice providers, nurses, medical assistants, technicians, and staff).

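### Adoption has no observation window, so its 6- and 12-month values rest on unequal post-rollout time and can appear to rise when referring has not changed

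*Protocol article*

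**What the plan says.** All references are to Phase 3 of the protocol article.

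- **Adoption measure** (Outcomes, Table 2): "Percentage of surgeons referring ÷ total surgeons in the pilot clinic". No period and no minimum number of referrals is given.
- **Adoption target** (same cell): "Target adoption: >75% of surgeons achieving >50% referrals". This is a proportion of referrals for each surgeon, a different quantity from the measure above it.
- **Maintenance** (Table 2): defined as "The extent to which pCGA use is sustained over the pilot period" and measured thus: "Trends in reach, adoption, and implementation outcomes will be evaluated at 6 months and 12 months". The table does not say whether each value is cumulative or covers only the preceding interval.
- **Timeline** (Study Design): "We will conduct a pretest-posttest pilot study of the implementation package over 10 months", and then "After an implementation rollout period of 2 months, postintervention data will be collected over 10 months".
- **Baseline** (Study Design): "We will collect baseline prepilot data via retrospective chart abstraction from the year before the intervention".

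The Self-Report Surveys section also uses 6 and 12 months, counted into the pilot. The Health Care Professionals section gives 12 referring surgeons across the two clinics.

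**The concern.** Whether a surgeon counts as referring depends on how long that surgeon is observed. Someone who refers one patient every six months will often be missed in a 4-month window and usually caught in a 10-month one. Dividing by a fixed number of surgeons does not correct for this.

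The trend in this share is meant to show whether use is sustained. If the later value rests on more observation time than the earlier one, a rise may reflect the calendar and not the surgeons. Adoption is one of two primary outcomes, and the pilot is meant to inform a larger implementation trial. A false impression of stable or growing adoption would carry into that planning.

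**Working it through.** The protocol states no expected adoption figure, so there is none to reproduce. The percentages below are illustrations.

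**Step 1: observation time behind each value.**

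| Reading of the 6- and 12-month points | Post-rollout data, first value | Post-rollout data, second value |
|---|---|---|
| From start of rollout, cumulative | 6 − 2 = 4 months | 12 − 2 = 10 months |
| From start of rollout, by interval | 4 months | 12 − 6 = 6 months |
| From end of rollout | 6 months | none: data stop at month 10 |

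A 6/6 split arises only if the two rollout months count as outcome data, which Study Design does not do. If the last reading were rescued by taking the second value at month 10, the intervals would be 6 and 4 months.

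**Step 2: model and inputs.** Let each of 12 surgeons refer at a constant Poisson rate r per month. The expected share with at least one referral in m months is 1 − exp(−r·m). The protocol gives no referral volume. I assume 20 to 40 referrals over 10 months, borrowing the enrolment figures of 20 (Recruitment and Enrollment) and 40 (Results, Phase 3). Then r = 20/(12×10) = 0.167 to 40/(12×10) = 0.333.

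**Step 3: results.** For example, at 20 referrals, 4 months gives 1 − exp(−0.667) = 48.7% and 10 months gives 1 − exp(−1.667) = 81.1%.

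| Scenario | 20 referrals | 40 referrals |
|---|---|---|
| Cumulative 4 then 10 months, constant rate | 48.7% to 81.1% | 73.6% to 96.4% |
| Cumulative, rate halved after month 6 (4 + 6/2 = 7 full-rate months) | 48.7% to 68.9% | 73.6% to 90.3% |
| Intervals of 4 then 6 months, constant rate | 48.7% to 63.2% | 73.6% to 86.5% |
| Same intervals, rate down 25% (6×0.75 = 4.5) | 48.7% to 52.8% | 73.6% to 77.7% |
| Same intervals, rate halved (6×0.5 = 3) | 48.7% to 39.3% | 73.6% to 63.2% |
| Intervals of 6 then 4 months, constant rate | 63.2% to 48.7% | 86.5% to 73.6% |

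On the cumulative reading the share cannot fall; if referring stopped altogether it would stay flat. On the 4/6 interval reading the break-even rate ratio is 4/6, so falls of less than one third still read as a rise. At 80 referrals the cumulative constant-rate shift shrinks to 93.1% to 99.9%.

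**Step 4: the >50% target.** Assume one eligible patient per surgeon-month, so 4 and then 10 patients. The chance that a surgeon exceeds 50% goes from 65% to 85% at a true referral probability of 0.7, from 18% to 17% at 0.4, and from 8% to 5% at 0.3. If the probability drops from 0.7 to 0.35 after month 6, the cumulative value falls from 65% to 34%. The target still depends on patient numbers, but it can show decay.

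**Step 5: reach.** Reach is referred ÷ potentially eligible patients. With a steady flow of eligible patients and referral halved after month 6, interval reach halves and cumulative reach falls to (4 + 3)/10 = 70% of its earlier value.

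**Step 6: baseline against pilot.** At the same rate, 12 against 10 months gives 86.5% against 81.1% (20 referrals) and 98.2% against 96.4% (40). This is a small bias against the package.

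**Step 7: equal windows.** With 5 and 5 months, constant referring gives 1 − exp(−0.833) = 56.5% in both windows at 20 referrals, and 81.1% in both at 40. If the rate halves, the values fall from 56.5% to 34.1% and from 81.1% to 56.5%. The artefact is gone.

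**The case against.** The strongest reply is that the unequal windows are inferred. The table speaks of surgeons referring, not of surgeons who have ever referred, and 6 and 12 months are evenly spaced. Whether a value is cumulative or by interval is commonly left to an analysis plan. This stands in part: the protocol does not prescribe an ever-referred count or unequal windows. But the article itself fixes the formula, the two time points and the 2 + 10 month timeline, and taken at face value these give no pair of equal post-rollout windows.

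A reader might infer that maintenance must show a rise even when referring falls. The documents do not support that. A rise under halved referring needs the cumulative reading; by 4/6 interval a halving shows as a fall, and 6/4 intervals would show a false fall.

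A reader might also infer that the pilot cannot detect decay. That is not so. Reach is trended at the same points and uses an eligible-patient denominator, and the >50% target can fall as well.

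The inputs are weak too. Enrolled patients are not referrals, more referrals would shrink the effect, and the two clinics are chosen to differ in referral habit, so equal surgeons is a simplification. With 12 surgeons, one surgeon is 1/12 = 8.3 points, so the interval shift of 49% to 63% is under two surgeons. Finally, maintenance carries no threshold or test, and the analysis is a descriptive pilot. These points limit the size and severity of the problem. They do not make the two adoption values comparable.

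**Conclusion.** The concern holds in limited form. The surgeons-referring measure has no window, and on the protocol's own timeline its 6- and 12-month values rest on unequal post-rollout time, or the second does not exist. Adoption can then appear to rise with no change in behaviour, by about 32 points cumulatively (49% to 81%) or 15 by interval (49% to 63%) at 20 referrals, and by 23 or 13 points at 40.

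These sizes rest on 20 to 40 referrals per 10 months, 12 equal surgeons and Poisson referring. That the cumulative share cannot fall does not depend on those assumptions. The problem is confined to this measure and to maintenance conclusions drawn from it. It should be corrected, but it does not undermine the pilot as a whole.

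**What to change.** 1. Reconcile the 6- and 12-month points in Table 2, and the matching survey times, with the 10-month data period, and state when month 0 is.
2. Score adoption in equal, non-overlapping post-rollout windows, for example months 1–5 and 6–10.
3. Base the adoption trend on referred ÷ eligible patients per surgeon in each window, the quantity behind the >50% target. Report separately the surgeons with no eligible patients in a window.
4. For the pre-post comparison of adoption, use a baseline window of the same length as the post-rollout one.

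The cost is mainly wording. Referral and eligible-patient counts are already needed for reach; they must be held by surgeon and date. The downside is fewer patients per surgeon in each window: at the assumed volumes, 20/(2×12) = 0.8 to 40/(2×12) = 1.7 referrals, so per-surgeon proportions will be coarse and should be shown with their counts.

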#### Self-Report Surveys

We will administer surveys to health care professionals (surgeons and pCGA staff) at 6 and 12 months into the pilot to assess the feasibility, acceptability, and appropriateness of the implementation package. We will contact health care professionals via email to complete the survey electronically; however, recognizing the demands of clinical schedules, a research assistant will make paper copies of the survey available for completion during clinic hours. We will use a previously validated survey instrument to measure implementation outcomes, specifically the acceptability, appropriateness, and feasibility of the intervention [94]. The self-report survey includes 4 items for each domain (12 items in total) and is estimated to take ≤15 minutes to complete (approximately 5 min/domain). Psychometric assessments of the instrument have demonstrated high validity (Cronbach α values ranging from 0.85 to 0.91) and high reliability (test-retest values ranging from 0.73 to 0.88). The items are scored on a 5-point scale. For each 4-item domain, the score can be calculated by averaging the responses. While cutoff scores have not been established, higher scores indicate greater acceptability, appropriateness, or feasibility.

#### Data Analysis

The aim of the pilot is to maximize reach and adoption while maintaining implementation fidelity before a full-scale implementation-effectiveness hybrid trial is conducted. The limited sample size will restrict our ability to evaluate differences in effectiveness outcomes such as mortality or morbidity; however, more proximal effectiveness estimates will be explored by abstracting short-term clinical outcomes (eg, medication changes at discharge). We will use exploratory measures to establish some preliminary point estimates for event rates and CIs within our sample for the purpose of planning a future study. As such, formal power calculations are not applicable to this pilot study. Recruitment data will inform the calculation of the reach, adoption, and maintenance outcomes. We will explore all RE-AIM outcomes for differences across underrepresented groups [69] (rural vs urban as determined by zip code, racial majority vs minority groups, men vs women vs other gender identities, and Hispanic vs non-Hispanic ethnicity). All data will be entered into Stata software (StataCorp LLC) for analysis. Data will be evaluated for accuracy and missingness. Descriptive univariate and bivariate analyses will be conducted, including chi-square tests for categorical data and 2-tailed *t* tests or Mann-Whitney *U* tests for continuous data as appropriate, with a cutoff of *P*<.05 for statistical significance.

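### The tests named for the Phase 3 pilot assume independent observations, but reach and adoption are compared before and after in the same two dissimilar clinics and largely the same surgeons, so their P values and intervals would be miscalibrated in either direction

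*Protocol article*

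**What the plan says.** The Phase 3 Study Design section of the protocol article sets the comparison: "We will conduct a pretest-posttest pilot study of the implementation package over 10 months, conducted at the clinic level at 2 busy academic medical center". The choice of the two clinics rests on their referral habits: "selecting one that does not routinely refer for pCGA in addition to one that does routinely refer". The baseline is historical: "We will collect baseline prepilot data via retrospective chart abstraction from the year before the intervention". The hypothesis is that the package "will improve the reach and adoption of the pCGA compared to the historic baseline".

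Under Outcomes, "The primary outcomes of this pilot trial will be reach and adoption". Table 2 measures reach as referred over potentially eligible patients, with a target above 50% in each clinic. It measures adoption with the surgeon as unit, with a target of more than 75% of surgeons each referring more than half of their eligible patients. The Health Care Professionals section gives the numbers: "Surgeons referring patients from the 2 clinics (n=12) and health care professionals engaged at the pCGA clinic (n=10").

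The Data Analysis section names the tests: "Descriptive univariate and bivariate analyses will be conducted, including chi-square tests for categorical data". For continuous data it lists 2-tailed t or Mann-Whitney U tests, and the cutoff is P<.05. It names no paired, clinic-stratified or surgeon-clustered method. It also says that power calculations do not apply, and that exploratory measures will give point estimates and confidence intervals for planning a later study.

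**The concern.** The chi-square and Mann-Whitney tests treat every observation as independent of every other. Three features of the pilot break that for the primary outcomes.

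- Two clinics chosen to differ in baseline referral are observed in both periods. Clinic is therefore a strong predictor of reach, and a test that ignores it uses the wrong variance.
- Patients are nested in about 12 surgeons, and the surgeon decides on referral. If surgeons change by different amounts, the effective sample size for the change in reach is closer to the number of surgeons than to the number of patients.
- Adoption is a yes/no state of a surgeon. Surgeons present in both periods give paired binary data.

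The pilot is meant to supply estimates for a multisite trial. Intervals on reach and adoption that are too wide or too narrow would carry over into that trial's planning.

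**Working it through.** The article gives no effect size or power figure, so there is none to reproduce. From the article come 2 clinics, 12 surgeons, the named tests and the .05 cutoff. **Every rate, variance, cluster size and clinic split below is an assumption.** The number of eligible patients, which is the denominator of reach, is not given.

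**1. Reach, stable clinic difference ignored (test too conservative).** Assume clinic rates of 10% and 60% and 30 eligible patients per clinic per period, so 60 per period.

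- Variance used by a pooled chi-square: 0.35 × 0.65 = 0.2275.
- True average within-clinic variance: (0.10 × 0.90 + 0.60 × 0.40)/2 = 0.165.
- SE of the difference: √(2 × 0.2275/60) = 0.087 assumed, against √(2 × 0.165/60) = 0.074 true.
- Null size: P(|Z| > 1.96 × √(0.2275/0.165)) = P(|Z| > 2.30) = 0.021. Simulation also gives 0.021, against 0.051 for a Cochran-Mantel-Haenszel test stratified by clinic.
- Power for +20 points in each clinic (simulated): 0.63 pooled, 0.73 stratified. At 50 per clinic: 0.86 and 0.92.

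**2. Reach, clinic volume shifts with no true change (test too liberal).** Same rates of 60% and 10%.

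- Busier clinic's share moves from 50% to 65%: 0.50 × 60 + 0.50 × 10 = 35% becomes 0.65 × 60 + 0.35 × 10 = 42.5%.
- Low/high clinic counts move from 35/25 to 25/35: pooled reach goes from 18.5/60 = 30.8% to 23.5/60 = 39.2%; the pooled chi-square rejects 12% of the time.
- Counts move from 40/20 to 20/40: from 16/60 = 26.7% to 26/60 = 43.3%; it rejects 48% of the time.
- The stratified test stays at 5% in both count examples.

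**3. Reach, surgeons differ in their change.** Simulated null size with 6 surgeons per clinic, between-surgeon SD of 1 logit, and equal numbers of patients per surgeon per period:

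| SD of surgeon change (logit) | Patients per surgeon-period | Pooled chi-square | Stratified by clinic | Paired t on 12 surgeon changes |
|---|---|---|---|---|
| 0.5 | 5 / 10 / 15 | 0.025 / 0.030 / 0.040 | 0.047 / 0.055 / 0.071 | 0.046 / 0.045 / 0.047 |
| 1.0 | 5 / 10 / 15 | 0.048 / 0.081 / 0.117 | 0.076 / 0.123 / 0.169 | 0.045 / 0.047 / 0.049 |
| 1.5 | 5 / 10 / 15 | 0.083 / 0.155 / 0.217 | 0.120 / 0.203 / 0.272 | 0.049 / 0.047 / 0.046 |

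With small variation in change the pooled test is still conservative. With larger variation it is liberal, and stratifying by clinic alone makes the size worse. Only the surgeon-level analysis holds its level throughout.

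**4. Adoption.** Assume 4/12 before, 9/12 after, five surgeons switching up and none reverting.

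- Uncorrected chi-square: 24 × (4 × 3 − 8 × 9)²/(12 × 12 × 13 × 11) = 4.20, P=.041.
- Exact McNemar: 2 × 0.5⁵ = .0625. Mid-p McNemar: half of that, .031.
- SE of the difference: independent √(4 × 8/12³ + 9 × 3/12³) = 0.185; paired √(5 − 25/12)/12 = 0.142.

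For a true change from 0.4 to 0.8 with within-surgeon correlation 0.4, simulated power is 0.57 for chi-square, 0.34 for exact McNemar and 0.56 for mid-p. At a null of 0.4 the sizes are 0.015, 0.003 and 0.012.

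**5. Staff surveys (secondary).** If the 6- and 12-month scores of the same people were compared by an unpaired test, the SE of change would be too large by 1/√(1 − r). With r set to the instrument's stated test-retest range, that is 1/√0.27 = 1.92 to 1/√0.12 = 2.89.

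**The case against.** The strongest reply is that the article does not commit to the faulty analysis. Its test sentence is introduced as descriptive, lists examples rather than a closed set, and follows closely on subgroup comparisons for which independent-sample tests are usual. The article is condensed, and a fuller analysis plan may specify pairing and clustering. This limits the severity but does not remove the point: the article names a test family and a significance cutoff, and nothing named fits paired or nested binary data. The qualifier about appropriateness reads as a choice between t and Mann-Whitney. A paired t could be meant by t tests, but both primary outcomes are proportions.

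Several stronger readings are tempting, and the article does not support them.

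- **That the clinics will be pooled.** This is an inference. The reach target is per clinic, which points the other way; but no clinic-stratified test is named for the pre-post comparison.
- **That power is lost on the primary outcomes.** That is one direction only. It fits reach with a stable clinic mix. For adoption, the paired tests do not gain power over the chi-square (0.34 or 0.56 against 0.57), and power is expressly disclaimed.
- **That the adoption conclusion flips.** It does with exact McNemar (.0625) but not with mid-p (.031), so part of the contrast is the conservatism of the exact test. The counts are invented.
- **That the staff surveys are a primary pre-post comparison.** They are taken only at 6 and 12 months, with no baseline, and their measures are not primary. No test of change is promised, and test-retest reliability need not equal a 6-to-12-month correlation.
- **That the same 12 surgeons make up the baseline year.** Likely, since the clinics are the same, but not stated.

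**Conclusion.** The point holds in limited form. The named tests do not fit a before-and-after comparison in two deliberately unlike clinics with patients nested in about 12 surgeons, and if followed as written they miscalibrate inference on both primary outcomes. The direction cannot be fixed in advance. Ignoring clinic or surgeon pairing makes intervals too wide (null size about 2% for reach; adoption SE 0.185 against 0.142). Ignoring variation in surgeons' change, or a shift in clinic volume, makes them too narrow (null size roughly 5% to 20% over the assumed ranges with surgeon-change SD of 1.0 or 1.5 logits, and 48% under a large mix shift).

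These sizes illustrate and do not predict, because the eligible counts, clinic rates and surgeon variation are all assumed. The pilot is also judged partly against fixed targets, which this does not touch. It is still worth correcting before the data are analysed, because the estimates and intervals are the pilot's product.

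**What to change.** In the Phase 3 Data Analysis section, or in the analysis plan if one exists, state:

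- **Reach:** the pre-post difference for each clinic, in line with the per-clinic target, plus a clinic-stratified difference whose interval allows for clustering by surgeon. One route is the surgeon-level paired changes, with the same weighting for estimate and interval so that both refer to one quantity.
- **Adoption:** for surgeons present in both periods, the paired transitions (started, stopped, unchanged), a paired-proportion interval, and a McNemar test with exact or mid-p chosen in advance. State how surgeons seen in one period only are reported.
- **Staff surveys (secondary):** if 6- and 12-month scores are compared, use a coded identifier and a paired t or Wilcoxon signed-rank test.

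The cost is analysis wording, recording the surgeon and clinic for each eligible patient in both periods, and a code on the survey form. No new patients or visits are needed. The price is that some intervals may widen: with a surgeon-change SD of 1 logit, the surgeon-level test has simulated power of 0.36 to 0.59 for a log odds ratio of 1, against 0.41 to 0.79 for the pooled chi-square, which at that SD holds its level at 5 patients per surgeon-period but not at 10 or 15.
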